**Figure 1 F1:**
[figure not shown]
Study flow chart.

### Sample size

We intend to recruit 100 participants, which is sufficient to detect a 1.5 kg difference between conditions, at 90% power and 5% type I error rate, while allowing for a 20% drop-out rate. Variance of weight change was based on results of a similar trial,^28^ which reported a SD of 2.13 kg at 2 months’ follow-up.

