### Statistical analyses

The statistical analysis of the primary outcome, effectiveness of the intervention for weight loss, will be carried out on the basis of intention-to-treat (ITT). That is, after randomisation, participants will be analysed according to their allocated intervention group. We will endeavour to obtain full follow-up data on every participant to allow full ITT analysis. A linear regression, predicting weight at 8 weeks’ follow-up while adjusting for baseline weight and GP practice, will assess the effect of condition.^37^ We will assess the sensitivity of the analysis to different assumptions about missing data using a variety of imputation methods, including baseline observation carried forward analysis and an analysis of participants completing follow-up. A final analysis will impute the last home-measured weight for people who did not attend the final follow-up. All tests will be done at a 5% two-sided significance level.

Secondary outcomes will be analysed in several ways. Adherence rates will be assessed and compared between the experimental and control condition. Moderator analyses will assess the effect of adherence, highest educational qualification, liking of weighing at baseline, and overall intervention rating at follow-up (only intervention condition) on weight change.

Further exploratory analyses may be added post-hoc based on preliminary findings. The statistical analysis plan can be found in online supplementary appendix 2.

10.1136/bmjopen-2019-031572.supp2Supplementary data

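### The stated sample-size inputs give about 88% power for 1.5 kg with 100 recruits, not 90%: a small shortfall that one sentence can correct

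*Protocol article*

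**What the plan says.** The Sample size section of the protocol article gives one complete numerical statement. The target is 100: "We intend to recruit 100 participants". The section presents this number as enough to show a 1.5 kg difference between the arms. The operating characteristics attached to it are "at 90% power and 5% type I error rate, while allowing for a 20% drop-out rate". The source of the variability is also given: "Variance of weight change was based on results of a similar trial". The SD taken from that trial is 2.13 kg, measured at two months.

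Two further inputs stand elsewhere in the article. Randomisation and blinding sets equal allocation to the two arms. Statistical analyses fixes the sidedness: "All tests will be done at a 5% two-sided significance level". The same section specifies the primary analysis as a linear regression of 8-week weight on condition, adjusted for baseline weight and GP practice. The Sample size section does not name the test behind the calculation, and it mentions neither a baseline correlation nor any reduction in variance from adjustment.

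**The concern.** Every quantity needed to check the sentence is printed, so the recruitment target should follow from the others. It does not. If one fifth of the participants are lost, the remaining 80 fall slightly short of the number that 90% power for 1.5 kg requires.

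What is at stake is the accuracy of the stated sensitivity. Study design and setting says that promising results would justify a longer randomised trial. The power statement may therefore be cited when this trial is interpreted or the next one is planned, and it should be reproducible from its own inputs.

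**Working it through.** **Inputs.**
- Difference 1.5 kg, power 90%, type I error 5%, drop-out 20%, SD 2.13 kg and 100 recruits (Sample size). The SD is taken as that of weight change, as the section indicates.
- Two-sided test (Statistical analyses).
- 1:1 allocation (Randomisation and blinding).

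**Attempt to reproduce 100.** For two equal groups, under the normal approximation:

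n per arm = 2 × (SD/difference)² × (z for 0.975 + z for 0.90)² = 2 × (2.13/1.5)² × (1.960 + 1.2816)² = 42.37, rounded up to 43.

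The t-test version gives 43.36, rounded up to 44. The completers needed are therefore 86 or 88. Allowing for 20% loss:
- normal: 86/0.8 = 107.5, so 108 recruits;
- t-test: 88/0.8 = 110 recruits.

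The stated 100 is 8 to 10 below this.

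**Power with 100 recruits and 20% loss.** This leaves 80 completers, 40 per arm.
- Standard error of the difference: 2.13 × √(2/40) = 0.476 kg.
- Normal: Φ(1.5/0.476 − 1.960) = Φ(1.19) = 88.3%.
- Noncentral t: 87.5%.

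The gap to 90% is 1.7 or 2.5 percentage points.

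**Difference detectable with 90% power at 40 per arm.**
- Normal: 0.476 × (1.960 + 1.2816) = 1.54 kg.
- t-test: 1.56 kg.

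**Drop-out at which 100 recruits still give 90% for 1.5 kg.**
- Normal: 1 − 86/100 = 14%.
- t-test: 1 − 88/100 = 12%.

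**Could a one-sided test explain 100?** A one-sided 5% test would need 88 to 90 recruits and would have about 93% power at 40 per arm, so 100 would be enough. The two-sided rule in Statistical analyses excludes this.

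**Could baseline adjustment explain it?** At 40 per arm, 90% power for 1.5 kg requires a residual SD of:
- 2.07 kg (normal), which means 1 − (2.07/2.13)² = about 6% of the variance of weight change explained;
- 2.04 kg (t-test), which means 1 − (2.04/2.13)² = about 8% explained.

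These shares correspond to a correlation between baseline weight and weight change of about 0.24 (√0.06) to 0.28 (√0.08). The article gives no such correlation. For illustration, an assumed correlation of 0.25 gives 90.2% (normal) or 89.5% (t), and 0.30 gives 91.0% or 90.3%.

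**The case against.** The strongest reply has four parts.

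*Rounding.* The difference is printed to one decimal. Under the normal approximation, 80 completers have 90% power for 1.544 kg, which prints as 1.5. That is fair as far as it goes, but it works under that formula only: the t-test figure, 1.563 kg, rounds to 1.6.

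*Planned analysis.* The primary analysis adjusts for baseline weight, so an unadjusted formula is normally conservative for it, and a modest gain would restore 90%. This stands as a reason to call the point minor. It does not rescue the sentence, because the calculation is said to rest on the variance of weight change and no further reduction is claimed.

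*Full follow-up.* The investigators intend to seek complete follow-up. With all 100 measured, 50 per arm, power would be about 94%. But the statement says that 90% holds with 20% drop-out allowed for, and that is the claim being checked.

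*Condensed source.* The article shortens a full protocol, and its analysis plan is in an appendix that is not shown. An assumption behind 100 may be recorded there. This lowers the certainty that a mistake was made, but the printed inputs still do not give the printed result.

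A reader might also infer that drop-out was allowed for by multiplying by 1.2 instead of dividing by 0.8. The article does not say how the allowance was applied, and the arithmetic does not support the inference. The required 86 or 88 completers times 1.2 give 103.2 or 105.6, that is 104 or 106 recruits. Only the unrounded normal figure comes near 100 (2 × 42.37 = 84.75; 84.75 × 1.2 = 101.7). The origin of 100 remains unknown.

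**Conclusion.** The sentence is wrong as printed, by a small amount. On its own inputs, with the two-sided 5% test and equal arms, 100 recruits and 20% loss give about 88% unadjusted power for 1.5 kg (88.3% normal, 87.5% t-test). The 90% figure belongs to a difference of 1.54 to 1.56 kg, to 108 to 110 recruits, or to drop-out of at most about 12 to 14%. The result assumes that 2.13 kg is the SD of weight change in both arms, that losses are equal between arms, and that adjustment brings no gain.

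A reader might conclude that the trial is underpowered or that a null result would be misread. The documents do not support that. The gap is about 2 percentage points, and a baseline adjustment explaining 6 to 8% of the variance of weight change would close it. A non-significant result would be read from its estimate and confidence interval, which a planned power of 88% rather than 90% would barely affect. The finding is about a stated figure, not about the adequacy of the design.

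**What to change.** Keep the target of 100 and correct the Sample size sentence in one of two ways.

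- If the calculation was unadjusted, restate it along these lines: *With 100 recruited and 20% lost, 80 participants will be analysed; this gives about 88% power for a difference of 1.5 kg, or 90% power for about 1.55 kg, assuming an SD of weight change of 2.13 kg and a two-sided 5% test.*
- If 100 rested on a gain from adjusting for baseline weight, say so and give the assumed value, either as a residual SD (2.04 to 2.07 kg would be needed) or as the share of variance explained (about 6 to 8%), with its source.

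The cost is one sentence and, in the first case, a slightly lower stated power. Recruitment, conduct and analysis do not change.

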### Randomisation and blinding

All eligible participants will be randomised with an allocation ratio of 1:1 to the intervention or control group. A randomisation sequence, stratified by GP and using block randomisation with randomly varying block sizes of 2 and 4 will be generated using a computer algorithm. Allocations will be concealed in numbered, sealed, opaque envelopes by an independent researcher in the department and handed to the researcher who will conduct the baseline visits.

Due to the nature of this trial, it will be difficult to blind participants to the treatment allocation. We will aim to make it as opaque as possible by presenting daily weighing as an intervention to control group participants, as done in previous trials.^29^ The researchers conducting baseline and follow-up will perform data analysis, and will not be blinded to treatment allocation. The primary outcome, weight change, will be measured objectively. Adherence to self-regulation steps will be measured objectively through the frequency of weight logs and completed questionnaires in control and intervention group. The evaluations of treatment components in the final questionnaire will be measured without researchers’ input and analysed quantitatively. Blinding of the researcher who conducts and analyses the semi-structured interviews with intervention group participants will not be possible.

### Intervention and control

#### Intervention

Participants will be asked to weigh themselves every morning after waking using standard body scales (Etekcity, California, USA) provided to them. In addition, they will be prompted to complete tasks which speak to the different steps of the self-regulation process, including (1) contextualising the weight measurement, (2) reflecting on behaviour and (3) planning weight loss actions. The individual tasks and their development are described in more detail below. Input from members of the public was sought at several stages of the intervention development.

Contextualising: In the think-aloud study participants struggled memorising daily measurements and keeping an overview of their weight loss progress, which impeded their ability to use weight measurements as constructive feedback. Participants stated they would have benefited from a weight tracking tool. Therefore, to support participants in contextualising their weight measurements, we will encourage them to use the app ‘Weight Loss Tracker, BMI’ by aktiWir GmbH. Research shows that digital tracking devices can significantly increase adherence to self-monitoring,^30 31^ perhaps because the visualisation of progress and feedback on weight loss success provides motivation and keeps users on track with their goals.^32^
Reflecting: The think-aloud study showed that participants struggled to interpret day-to-day weight changes due to daily fluctuations that were not caused by fat loss or gain.^12^ We therefore decided to encourage reflection on a weekly rather than daily basis. Participants will receive weekly emails with feedback on their weekly weight trends, asking them to complete an online questionnaire (Qualtrics, USA). The questionnaire will prompt reflection on the relationship between behaviours performed throughout the week and weight change observed. Participants will be asked to use this insight to evaluate the use of the weight loss actions they had performed throughout the week.Action Planning: We aimed to strike a balance between ensuring that participants choose appropriate actions and allowing them to choose actions themselves, as lack of goal ownership predicts attrition.^23^ Participants will therefore choose one weight loss action per day from a list of 53 actions (see online supplementary appendix 1). To create the actions list, we first identified weight loss actions from effective weight loss interventions in the literature. These were reviewed, adapted and complemented during iterative brainstorming sessions with an interdisciplinary expert team, comprised of dietitians, GPs and psychologists. The rationale for daily action plans was twofold: (1) allowing participants to adapt their actions flexibly to their day and (2) giving participants exposure to a wider range of strategies. Based on action planning and implementation intention research, which shows that the specificity of action plans increases likelihood of implementation,^33–35^ we will ask participants to specify where, when and how they will perform their chosen action, which cues they will use, which barriers they might experience and how they will deal with them.As participants only reflect on their behaviour on a weekly basis, we grouped the actions conceptually into seven categories, five of which cover diet-related actions and two of which cover physical activity-related actions. Participants will be asked to choose one category at the beginning of the week, and choose daily actions from this category for the rest of the week. Weekly behaviour reflection will therefore focus on the effectiveness of a category of actions. Taken together, the reflection and action planning process shall enable participants to experiment with different weight loss approaches and decide on their effectiveness and usefulness based on trends in weight data. At the beginning of weeks two through eight of the intervention, participants will be prompted to commit to some of the actions of previous weeks, as the performance of several weight loss actions increases chances for weight loss. Action planning support will be provided through daily questionnaires (Qualtrics, USA), which will be sent to participants every morning via email.

10.1136/bmjopen-2019-031572.supp1Supplementary data

At baseline, participants will receive detailed instructions about the intervention with the aid of a manual which they may take home afterwards. The manual will explain the rationale of self-regulation and experimentation to participants and give tips on how to best weigh on a daily basis. It will also provide information on the different weight loss actions participants can try throughout the study. Participants will also be given an action diary, in which they will be asked to record their performed weight loss actions.

We will call participants at the end of the first and fourth week to ask about and solve any technical problems that may have arisen (eg, with the functioning of the scales or the receiving of questionnaires). A figure from the study manual depicting the intervention procedure is displayed in figure 2. The Template for Intervention Description and Replication (TIDieR) checklist^36^ for the PREVAIL intervention and the comparator is reported in table 1.

**Figure 2 F2:**
[figure not shown]
Intervention procedure as depicted in study manual.

**Table 1 T1:** TIDiER checklist describing the intervention and control condition

	Intervention: PREVAIL	Control: daily self-weighing without behavioural support
Brief name	PREVAIL (*P*eople *Re*gulating Themsel*v*es to *A*chieve We*i*ght *L*oss)	Self-weighing only
Why	*Self-weighing:* Monitoring weight on a daily basis will enable participants to take note of their weight loss progress. *Weight* *t* *racking:* Our preceding study^12^ found that people can lose track of their weight loss progress when weighing every day because they struggle to remember measurements. We therefore ask participants to track their weight. *Action planning:* In our preceding study, participants rarely made action plans to help them progress with their weight loss.^12^ If they did make action plans, they were rarely specific. Specificity of action plans is a significant predictor of the likelihood of implementation.^33–35^ We therefore guide participants through a specific action planning process. *Report email:* Participants in our preceding study struggled to see trends in their weight data.^12^ Unfortunately, the app we are using for weight tracking does not provide users with trend information. We will therefore send out weekly emails, containing information on the trend of the weight measurements of the last week. *Reflection and action evaluation:* Our preceding study revealed that daily fluctuations vary over time within people, making it difficult to interpret daily weight changes. We therefore want to encourage participants to reflect on their weight changes and the effectiveness of their weight loss actions on a weekly basis. Using the weekly weight trend information, participants will be able to evaluate whether they found the group of actions they performed effective and worth repeating.	A previous trial has found that self-monitoring of weight without further guidance is not effective for weight loss.^11^
What	*Self-weighing*: Participants will be instructed to weigh themselves daily using simple digital body scales (Etekcity Corporation, California). They will be asked to weigh themselves in a similar state every day, ideally first thing in the morning and without clothes. *Weight tracking:* Participants will be asked to download the free app “Weight Loss Tracker, BMI” by aktiWir GmbH on their smartphone and use it on a daily basis to record their weight measurements. They will be asked to submit a backup of their data to the research team every week. *Action* *p* *lanning:* Participants will receive a daily questionnaire helping them to plan a weight loss action. The questionnaire will start by asking participants to enter their morning weight. At the beginning of first week, they will then be asked to choose a category of actions, and they will be able to choose one of the actions within this category per day for the rest of the week. There are seven categories in total, five covering diet-related actions and two covering physical activity-related actions. Participants will be asked to specify for each action how, when and where they are going to perform it, and which cues they are going to use. They will also be prompted to think about how to overcome potential barriers. At the start of weeks 2 through 8, participants will be encouraged to try out a new category of actions. We will additionally ask participants on a weekly basis to commit to continuing some of the actions they tried out in previous weeks. In order to help participants to maintain an overview of the actions they performed so far, we will provide them with a non-digital action plan diary. *Report email:* Once a week, participants will receive an email from the research team, informing them about their trend weight change for the last week. This trend weight change consists of the slope of a trend line fitted across all measurements of the week, multiplied by the number of days covered by the measurements. The weight measurements used to create these reports will be taken from the daily action planning questionnaires. *Reflection and* *a* *ction* *e* *valuation:* In the weekly report email, participants will receive a link to the reflection and action evaluation questionnaire. This questionnaire prompts participants to think about why their weight has changed as it has. They are further asked to evaluate the group of actions they performed across the week, including whether they found them useful and whether they would repeat them. On the basis of this evaluation, participants will be able to decide which actions they want to continue doing in the next weeks, and which ones to drop. Using this method of self-experimentation, participants will be able to try and test different weight-loss strategies and identify the ones that are effective and sustainable for them.	Self-weigh every morning in a similar state, using smart scales (BodyTrace, New York).

#### Control

Participants in the control group will be instructed to self-weigh daily and see what daily weighing motivates them to do. They will not receive any further instructions. By using this comparator group, we want to test whether the self-regulation process can enhance self-weighing to be an effective weight loss tool. Participants will receive smart scales (BodyTrace, New York) which are equipped with a SIM card and automatically transfer measurements to a secure server via the 3G/4G network. This will allow us to assess adherence to daily weighing in the control group.

### Patients and public involvement

Members of the public were involved in the design of the study at several stages. After creating the invitation letter, PIS, informed consent form, semi-structured interview guide and the baseline, daily, weekly and follow-up questionnaires for the PREVAIL intervention, we asked members of the public for feedback. Our department has a panel of >100 members of the public with an interest in weight management. Based on phone calls with members of this panel we were able to make the materials clearer and more concise. The manual, explaining the intervention in detail, was further discussed with members of the panel in a focus group session. As a result of this focus group session, the manual was professionally edited to be shorter. We also added figures and graphs to present the procedures of the study more visually. The panel helped to revise the explanations of the different action plans.

A test run of 4 weeks was conducted with five members of the department, who are not otherwise involved in this study. They provided feedback on the running of the intervention which, among other outcomes, led to the creation of a reminder email which will be sent out before the start of the intervention.

No members of the public will be involved in conducting or analysing the study. However, we will gather input on the most suitable and effective ways to disseminate our research findings to the public.

### Outcomes

#### Primary outcome

Change in body weight between baseline and follow-up by condition.

#### Secondary outcomes (process evaluation)

Adherence to self-regulation steps, assessed through weight records and daily action planning/weekly evaluation questionnaires.Test moderators of effectiveness: adherence measures, highest educational qualification, liking of weighing at baseline, overall rating of intervention in final questionnaire.Perceived effectiveness of intervention and liking of intervention features based on final questionnaire and follow-up interviews.Barriers and unmet needs for successful weight loss, assessed in follow-up interviews.

### Measurements

A schedule of measurements can be found in table 2.

**Table 2 T2:** Schedule of measurements

	Screening	Baseline visit	Intervention period	Completion email	Follow-up visit (after 8 weeks)
Length	10 min	Up to 1 hour	10 min per day	5 min	up to 45 min
Who conducts	Research team	Research team	Participants	Research team	Research team
Eligibility assessment	☑	☑ (BMI)			
Enrolment		☑			
Baseline questionnaire		☑			
Weight		☑	☑		☑
Height		☑			
Allocation		☑			
Weight tracking (only intervention)			☑		
Daily questionnaire (only intervention)			☑		
Weekly report and questionnaire (only intervention)			☑		
Final questionnaire (only intervention)				☑	
Semistructured interview (20 participants in intervention group)					☑

BMI, body mass index.

